### 3.3. Statistical analysis

To measure the effect of the intervention within each group, and in the same group before and after intervention, the effect size will be calculated using Cohen d,^[47]^ which classifies effect size as small (0.2–0.5), moderate (0.5–0.8), or large (>0.8). Lastly, logistic regression models will be used to measure the impact of the intervention on improved quality of life by adjusting for any variables that may be considered confounding variables from a clinical point of view.

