**Methods::**

Mixed-methods study based on a randomized clinical trial and qualitative analysis with a descriptive phenomenological approach. The study will be conducted in primary care in Catalonia. The control group will follow the usual clinical practice and the intervention group the usual practice plus the studied intervention (12 hours over 4 days). The intervention based on nutrition, chronobiology and physical exercise will be designed considering participants’ opinions as collected in 4 focus groups. To evaluate effectiveness, EuroQol-5D, multidimensional fatigue inventory, VAS pain, Pittsburgh Sleep Quality Index, erMEDAS-17, biological rhythms interview of assessment in neuropsychiatry, REGICOR-Short, FIQR and Hospital Anxiety and Depression Scale questionnaires will be collected at baseline, and at 1, 3, 6, and 12 months post-intervention. Food intake, body composition, resistance and, strength will also be evaluated. The effect size will be calculated using Cohen d and logistic regression models will be used to quantify the impact of the intervention by adjusting for different variables.

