## 2. Methods

### 2.1. Study design and intervention description

Study design: Mixed-methods study that includes a nonblinded, pragmatic randomized clinical trial with parallel groups and a qualitative study with 4 focus groups (two pre-intervention and 2 post-intervention) with a descriptive phenomenological approach. The control group will follow the usual clinical practice, consisting of an individual visit with the FM specialist, who will conduct a standardized medical history and inform the patient of the disease using a custom designed leaflet.^[33]^ The intervention group will follow the usual practice plus the intervention under study (Fig. 1).

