## 3. Quantitative study

### 3.1. Study variables

Main dependent variable: The main variable to be evaluated will be quality of life, assessed with the EuroQol-5D questionnaire.^[35]^

Secondary dependent variables: Fatigue will be assessed with the multidimensional fatigue inventory,^[36]^ consisting of 20 items and several dimensions. Sleep quality and insomnia will be evaluated with the Pittsburgh Sleep Quality Index-19 items.^[37]^ The VAS questionnaire will be used^[38]^ to assess pain. Adherence to the Mediterranean diet will be evaluated with the 17-item erMEDAS questionnaire.^[39]^ Physical exercise and sedentary lifestyle will be assessed with the REGICOR short questionnaire.^[40]^ In addition, circadian biological rhythm will be assessed with the biological rhythms interview of assessment in neuropsychiatry questionnaire,^[41]^ and anxiety with the Hospital Anxiety and Depression Scale.^[42]^ Moreover, people diagnosed with FM will be assessed with the FIQ-R.^[43]^ Food intake will also be evaluated using 24-hour reminders and a FFQ.^[44]^ Body composition will be analyzed through bioimpedance, strength and endurance using various validated tests, such as the 6-min walk test, the 30 second sit to stand test and hand dynamometer measurements.^[45]^

Independent variables: Sociodemographic variables (sex, age, educational level, profession, employment situation, size of city of residence, and comorbidity).

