### 3.2. Data collection

Sample size and sampling procedure: The sample size was calculated by GRAMNO V7.12. sample size calculation program and is based on the variations we expect to observe in the EuroQol-5D questionnaire on health-related quality of life.^[35]^ Accepting an alpha risk of 0.05 and a beta risk of <0.05 in a 2-tailed test, a minimum of 43 subjects are needed in each group to detect a minimum difference of 1.6 between 2 groups, with a standard deviation of 1.8. The loss to follow-up rate was estimated at 20%.

Patients diagnosed with FM (ICD-10 code M79.7) with or without CFS (Myalgic encephalomyelitis, code G93.3) treated at Terres de l’Ebre ICS Primary Care (Catalonia) and who meet inclusion criteria will be contacted by phone and invited to participate in the study. Patients will be asked to come to the health center for the first visit, where the study will be explained, and informed consent signatures will be collected. A randomization list will be generated following Efron procedure^[46]^ and using the statistics program SPSS. At this visit, the patient will be informed of which group they will participate in (control or intervention) and the schedule of sessions (or visits). Additionally, the baseline data will be collected from self-administered questionnaires (EuroQol-5D, multidimensional fatigue inventory, VAS pain, Pittsburgh Sleep Quality Index, erMEDAS-17, biological rhythms interview of assessment in neuropsychiatry, REGICOR-Short, FIQR, Hospital Anxiety and Depression Scale) using Microsoft Forms or paper if participants have difficulty using technology. These data will be collected again at 1, 3, 6, and 12 months post-intervention (Table 1). Data will also be collected in person at baseline and at 3 and 6 months post-intervention to evaluate the food intake, body composition, strength and endurance of study participants. These data will be collected from both the intervention and control groups and will be entered into an Excel database for use in the various analyses.

**Table 1 T1:** Data collection planning.

Data collection	Baseline	1m post	3m post	6m post	12m post
To assess quality of life and symptoms, chronobiology and healthy habits (ONLINE):					
*EuroQol-5D: quality of life*	X	X	X	X	X
*MFI (20-items): fatigue*	X	X	X	X	X
*VAS pain: visual analogue pain intensity scale*	X	X	X	X	X
*PSQI (19 items): sleep quality*	X	X	X	X	X
*BRIAN: biological rhythm*	X	X	X	X	X

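### The stated effect size is a within-group before/after Cohen d; no between-arm estimate on the EuroQol-5D scale used for sizing is stated

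*Protocol article*

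**What the plan says.** Section 2.1 describes a "nonblinded, pragmatic randomized clinical trial with parallel groups". Section 3.1 fixes the outcome: "The main variable to be evaluated will be quality of life, assessed with the EuroQol-5D questionnaire". Section 3.2 sizes the trial to "detect a minimum difference of 1.6 between 2 groups", with a standard deviation of 1.8, and gives the error rates as "Accepting an alpha risk of 0.05 and a beta risk of <0.05 in a 2-tailed test". The result is 43 per group, with 20% loss to follow-up. The same section collects the questionnaires from both arms at baseline and at 1, 3, 6 and 12 months.

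Section 3.3 then names two analyses:

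- **Effect size.** It opens "To measure the effect of the intervention within each group, and in the same group before and after intervention" and continues "the effect size will be calculated using Cohen d". The bands are small (0.2 to 0.5), moderate (0.5 to 0.8) and large (above 0.8).
- **Regression.** It says "logistic regression models will be used to measure the impact of the intervention on improved quality of life by adjusting for any variables" that are clinically plausible confounders. The abstract words this more generally: "logistic regression models will be used to quantify the impact of the intervention by adjusting for different variables".

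**The concern.** The effect-size sentence presents a before/after change within an arm as the effect of the intervention. Such a change does not use the randomisation. It combines any effect of the programme with everything else that moves a patient's score between two visits.

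The article itself describes several such sources. The Introduction says the disease runs in flare-ups, section 2.1 says the trial is not blinded, and section 2.1 gives the control arm a specialist visit and a leaflet. Patients who enroll during a bad spell will also tend to drift back towards their usual level.

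A d built from that change is then graded small, moderate or large, and a reader would take the grade as the size of the programme's benefit. The trial would also be sized for one quantity, a difference between two means, and report others: a within-arm d and an odds ratio for a binary outcome.

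**Working it through.** **1. What the sample size was calculated for.** Inputs from section 3.2: difference 1.6, SD 1.8, two-sided alpha 0.05, beta 0.05 (power 95%), loss 20%.

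- Standardised target: 1.6 / 1.8 = 0.89.
- Two-sample formula, normal approximation: n = 2 × [(1.960 + 1.645) × 1.8 / 1.6]² = 32.9, so 33 per group.
- With the noncentral t distribution: 34 per group, power 95.1%.
- Allowing for loss: 34 / (1 − 0.20) = 42.5, so 43 per group. This is the plan's figure.
- For contrast, a paired before/after test of 1.6, assuming a change SD of 1.8: n = [(1.960 + 1.645) × 1.8 / 1.6]² = 16.4, so about 17 in one group.

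The 43 is therefore a between-arm calculation. It is not a sizing for within-arm change.

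**2. What the planned analyses estimate.**

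| Place | Quantity | Contrast |
|---|---|---|
| 3.2, sample size | Mean EuroQol-5D difference of 1.6 | Between arms |
| 3.3, first sentence | Cohen d, before to after | Within an arm |
| 3.3, second sentence | Improved quality of life (binary), logistic model | Between arms, on its natural reading |

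No row of section 3.3 matches the row from section 3.2.

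**3. What the within-arm d shows when the intervention does nothing.** Let both arms shift by the same amount c, in units of the baseline SD, so that the true between-arm effect is zero. The article gives no value for c, so a range of 0.2 to 0.8 is assumed.

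- If d is mean change divided by the baseline SD, its expected value is c: 0.2, 0.5 or 0.8.
- If d is mean change divided by the SD of the change, it is c / √[2(1 − r)], where r is the pre-post correlation. At an assumed r of 0.5 this is again 0.2, 0.5 and 0.8. At r = 0.7 it is 0.26, 0.65 and 1.03.
- The between-arm d is 0 throughout.

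On the article's own bands, an ineffective programme could thus be graded anywhere from small to large, depending only on the shared shift.

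**4. Whether the logistic model fills the gap.** Assume normal scores, the target d of 0.89, and a cut at the midpoint between the arms.

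- Proportions improved: Φ(−0.444) = 0.328 and Φ(0.444) = 0.672, a difference of 0.343.
- Power with 34 per arm: Φ[(0.343 − 1.96 × √(2 × 0.25 / 34)) / √(2 × 0.328 × 0.672 / 34)] = Φ(0.93) = 82%.
- Comparison of means, same approximation: Φ(0.889 × √(34/2) − 1.96) = Φ(1.705) = 95.6%.

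So even where it applies, the binary analysis does not deliver the power for which the trial was sized.

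**5. What baseline adjustment gains.** Against a comparison of follow-up means, the variance factor is 1 − r². At r = 0.5 it is 0.75 and at r = 0.7 it is 0.51, a reduction of 25% to 49%.

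**The case against.** A reader might infer that the randomised comparison is never estimated at all. The article does not support that. Section 3.3 and the abstract both give the impact of the intervention to logistic regression. With outcomes collected in both arms, randomised group is the natural exposure in that model.

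A reader might also infer that benefit will be claimed because one arm changed significantly and the other did not. No within-arm significance test and no such decision rule is stated. Nor does the article call Cohen d its primary result. Because d is computed in each arm, the control value would stand beside the intervention value, and a shared drift would be visible.

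The sentence may also be a slip. As written, its two halves say nearly the same thing, and the abstract mentions Cohen d without restricting it to one arm. The authors may have meant between groups in the first half. Finally, this is a condensed article, and model details commonly sit in an analysis plan that is not shown.

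These points narrow the concern but do not remove it. The article is not silent here: it states a contrast, and the wrong one. If that is a slip, it still has to be corrected, because anyone following the text would compute a before/after d. Two within-arm values side by side give neither an estimate nor an interval for their difference. Section 3.3 ties the logistic model to quality of life only, so for fatigue, pain, sleep and the other scores the within-arm d is the only analysis it describes.

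**Conclusion.** The concern holds in this limited form: the stated effect size is within-group, and no between-arm estimate on the EuroQol-5D scale is stated, although the trial is sized on one. The mismatch between sections 3.2 and 3.3 follows from the text and from reproducing the 43 per group, and needs no outside assumption.

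The size of the distortion does rest on assumptions. It equals whatever shift the two arms share, shown here for an assumed 0.2 to 0.8 SD. The 82% against 95.6% power comparison assumes normal scores and a midpoint cut, since the article does not define improvement. At the trial's own target of 0.89, 34 evaluable patients per arm already give about 95% power for a difference in means, so the sample size is adequate for the analysis that should be stated.

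**What to change.** Replace the effect-size sentence in section 3.3 with text to this effect:

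- The effect of the intervention is the between-arm difference in mean EuroQol-5D score at one named follow-up visit. It is estimated with a linear model adjusted for baseline EuroQol-5D, with participants analysed as randomised, and reported with a 95% CI.
- Cohen d is that difference divided by the pooled baseline SD.
- The same model is used for the continuous secondary outcomes.
- Within-arm changes are descriptive, and the logistic model is supportive.

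The sponsor has to choose the visit from those already scheduled and should record it before outcome data are examined. The cost is the wording of section 3.3. Baseline and follow-up scores are already collected in both arms, and 43 per group stands. Baseline adjustment can only help precision: a variance reduction of 25% to 49% at an assumed pre-post correlation of 0.5 to 0.7.

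### The sample size is for a difference in mean EuroQol-5D, but the only inferential model named is a logistic regression on improvement, for which the stated 95% power does not hold

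*Protocol article*

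**What the plan says.** EuroQol-5D is the main dependent variable (section 3.1). The sample size in section 3.2 is set by "Accepting an alpha risk of 0.05 and a beta risk of <0.05 in a 2-tailed test", and allows for a 20% loss to follow-up. The 43 per group are those required "to detect a minimum difference of 1.6 between 2 groups", and the SD assumed is 1.8. These are the inputs of a two-sample comparison of means.

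Section 3.3 names two analyses. The first is Cohen d, described as within each group and before versus after in the same group. The second is the model for the effect of treatment: "logistic regression models will be used to measure the impact of the intervention on improved quality of life". No fixed list of covariates goes with it; the text speaks only of "adjusting for any variables that may be considered confounding variables from a clinical point of view". The abstract names the same pair of analyses, and its wording for the second is "logistic regression models will be used to quantify the impact of the intervention by adjusting for different variables". Neither place mentions a t-test, an ANCOVA, a mixed model or any other comparison of means between arms.

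**The concern.** A power statement belongs to one particular test. Here it was worked out for a comparison of means, while the model that is to measure the effect of the intervention has a binary outcome. Splitting a continuous score into improved and not improved discards information, so the same patients give less power. If the logistic model is taken as the main analysis, the trial runs a larger risk of missing the effect it was designed to find than the 5% that the protocol states.

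The adjustment wording adds a smaller difficulty. In a randomised trial, allocation deals with confounding, and covariates are there for precision. A rule that admits whatever might be judged a confounder does not direct the model to the covariate that usually helps most, the baseline value of the outcome.

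**Working it through.** **Inputs (section 3.2).** Difference 1.6, SD 1.8, two-sided alpha 0.05, power 95%, loss 20%. The standardised difference is d = 1.6/1.8 = 0.889.

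**Reproducing 43 per group.** Normal approximation: n = 2 × [1.8 × (1.960 + 1.645)/1.6]² = 32.9, so 33 per arm. The exact t calculation gives 34 per arm, with 95.1% power. Allowing for loss, 34/0.80 = 42.5, so 43. The stated figure is therefore right for a t-test on means and already includes the 20% loss. About 34 per arm are expected to be evaluable.

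**The same data as a binary outcome.** Assume normal scores with SD 1.8 and means 1.6 apart, and call a patient improved above a cut c, measured in SDs from the control mean. Then p0 = 1 − Φ(c) and p1 = 1 − Φ(c − d). With p̄ the average of p0 and p1,

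power = Φ{[(p1 − p0)√n − 1.96√(2p̄(1 − p̄))] / √(p0(1 − p0) + p1(1 − p1))}.

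At the midpoint cut, c = 0.444, p0 = 0.328, p1 = 0.672 and n = 34. The numerator is 0.343 × 5.831 − 1.96 × 0.707 = 0.616 and the denominator is 0.664. The ratio is 0.927 and power is 82%.

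| Improved, control v intervention | Power, 34 per arm |
|---|---|
| 33% v 67% | 82% |
| 30% v 64% | 82% |
| 20% v 52% | 80% |
| 50% v 81% | 79% |
| 10% v 35% | 69% |
| 70% v 92% | 65% |

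Exact enumeration for an unadjusted logistic model, over a fine grid of cuts, gives a maximum of 83% (likelihood-ratio test) or 81% (Wald test). At 7% v 29% improved it falls to about 53 to 67%, depending on the test. With all 43 per arm retained the maximum is about 90%, against 98% for the t-test. Holding 95% power over the cuts in the table takes 53 to 79 completers per arm. That is 53/0.80 = 67 to 79/0.80 = 99 randomised per arm.

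**Improvement defined on change from baseline.** This needs two assumptions that the document does not give: improvement means a change above 0.5 SD, and 1.8 is the SD of a score at one time point. With a pre-post correlation r = 0.6, the SD of change is √(2 × 0.4) = 0.894 SD units. Then p0 = 1 − Φ(0.5/0.894) = 0.288 and p1 = 1 − Φ((0.5 − 0.889)/0.894) = 0.668. Simulated power for the logistic model is about 87 to 89%, and exact enumeration without covariates gives 88 to 90%. The unadjusted comparison of means has 95%. For ANCOVA the effective d is 0.889/√(1 − 0.36) = 1.11, and power is 99%.

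This case is sensitive to r. At r = 0.5 the SD of change is 1.0, p0 v p1 is 0.309 v 0.651, and power is 80 to 83%. At r = 0.7 the SD of change is 0.775, p0 v p1 is 0.259 v 0.692, and power reaches 95 to 96%. ANCOVA at r = 0.7 has effective d = 0.889/√(1 − 0.49) = 1.24 and power above 99%.

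**The case against.** The strongest reply is that this is a condensed article. A full analysis plan may define improvement, list the covariates and add a comparison of means. The missing cut-off and covariate list are details that an article commonly leaves out, and they are no fault here. What remains is a conflict inside the text itself: it states one basis for the sample size and another model for the effect. A fuller plan that adds a comparison of means would still leave this text to be corrected.

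Cohen d may also have been meant between groups. Read literally, the two phrases of that sentence say the same thing twice, and the abstract sets no within-group limit. So one cannot say that the logistic model is the only between-arm quantity, and the text does not call it primary. But an effect-size index is not a test, and the stated alpha and beta cannot attach to it.

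Three stronger readings are tempting and are not supported:

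- *Overfitting will inflate the odds ratio.* Section 3.1 lists "Sociodemographic variables (sex, age, educational level, profession, employment situation, size of city of residence, and comorbidity") as independent variables, but nowhere says that all will be entered. In simulation the median odds ratio is about 5.1 with no irrelevant covariate parameters, about 6.4 with 7, and 7.6 to 8.0 with 12. That is a conditional risk only.
- *Baseline EuroQol-5D is left out.* An open rule excludes nothing, and the score is collected at baseline.
- *The choice of cut-off and adjusters leaves the result open to steering.* That presumes that no fuller document fixes them.

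**Conclusion.** The mismatch stands. The sample size is arithmetically correct for a comparison of means, but the stated type II error below 5% does not carry over to the logistic model that the text names. Where the quantity being cut has the protocol's own SD of 1.8 and is normal, no cut reaches 95%. Power with 34 per arm is at most about 80 to 83%, about 65 to 80% at less central cuts, and lower at extreme ones. With no loss it is at most about 90%.

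The size of the loss is a range, because the cut-off is unstated. A reader might infer a single figure, such as a type II error three to four times the stated one. That fits only the favourable cuts (17 to 20% against 5%). Across the definitions examined above, the ratio runs from roughly 2 (the change definition at r = 0.6) to 9 (the strictest cut). At a correlation near 0.7 the change definition would reach the target. That would rest on a correlation the document does not give, and the comparison of means is stronger still under the same assumption. Confidence is high for the mismatch and moderate for its size.

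**What to change.** In section 3.3 and the abstract, name as the primary between-arm analysis a linear model (ANCOVA or a mixed model) of the continuous EuroQol-5D score, with arm and baseline EuroQol-5D. Add at most a short, pre-stated set of prognostic covariates. Replace the open wording about possible confounders with that list, and say that the adjustment is for precision. Keep the logistic model of improvement as a secondary analysis.

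If the logistic model is to stay primary, restate the power of 43 per group on the proportions expected to improve in each arm.

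The first option is a change of wording. EuroQol-5D is already collected at baseline and at every follow-up, and 43 per group remains adequate under the stated assumptions. The small downside is that an odds ratio for improvement is no longer the headline figure. The second option means accepting lower stated power or, at the cuts tabulated above, randomising about 67 to 99 per arm to keep 95%.

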## 1. Introduction

Fibromyalgia (FM) and chronic fatigue syndrome (CFS) are considered central sensitization syndromes and involve neurological, metabolic and immunological circuits. Widespread pain, fatigue, and insomnia are the main symptoms of these conditions and seriously affect quality of life, especially in women.^[1]^

The etiopathogenesis of FM remains unclear and controversial,^[2]^ and there are currently no biomarkers or specific medical tests available for it.^[3]^ The prevalence of FM is estimated to be between 0.02% and 6.6% globally^[4]^ and 2.45% in the Spanish population.^[5,6]^ The annual cost per patient in industrialized countries is estimated to be €7256 to €7900, and the indirect costs (loss of productivity) are considered greater than direct ones (medical visits, prescriptions, etc).^[6]^ FM thus represents a high cost for society, estimated at €12.9 million in Spain in 2017.^[7]^

CFS, which often overlaps with FM,^[8,9]^ affects all ages and socioeconomic groups, although it is most common in the 30 to 50 age group. The estimated prevalence in the United States is 0.42%, of which 70% are women.^[10]^ This represents an annual cost of $17 to $24 million.^[11]^ There are no updated data on the incidence of CFS in Europe, but it is estimated to currently affect around 2 million people.^[12]^

The pharmacological treatments currently used in FM are only partially effective, and patients do not improve as expected. The disease becomes chronic and presents in the form of flare-ups, resulting in no positive impact either for patients or the healthcare system. Therefore, recent research on FM treatment focuses on evaluating non-pharmacological multicomponent interventions that involve various disciplines (physical therapy, psychology, and health education).^[6]^ The results of this type of multidisciplinary treatment are positive and have been shown to decrease pain and improve quality of life.^[13,14]^ These interventions were mainly based on cognitive-behavioral therapy, physical activity, and health education, often with very limited or no emphasis on nutrition or chronobiology.

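### EuroQol-5D is measured at four follow-up visits, but the only between-arm model named is a logistic regression that nothing links to the repeated measurements; a mixed model would be a cheap improvement

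*Protocol article*

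**What the plan says.** Section 3.1 of the protocol article makes quality of life on the EuroQol-5D the main dependent variable. Section 3.2 says of the questionnaires, after the baseline collection: "These data will be collected again at 1, 3, 6, and 12 months post-intervention". Table 1 agrees, giving four follow-up values per patient. (Section 2.1 lists only 1, 3 and 6 months; this note uses the fuller schedule of section 3.2, Table 1 and the abstract.)

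Section 3.3 names two analyses. One is Cohen d, within each group and before versus after. The other is the only model: "logistic regression models will be used to measure the impact of the intervention on improved quality of life", adjusted for clinically chosen confounders. The abstract repeats both. Neither place names the visit to which the model applies or says how several values from one patient enter it.

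On size, section 3.2 assumes an SD of 1.8, tests two-sided at 0.05, asks for power above 95%, and concludes: "a minimum of 43 subjects are needed in each group to detect a minimum difference of 1.6 between 2 groups". On attrition, the same section says: "The loss to follow-up rate was estimated at 20" per cent. Section 2.1 describes a "nonblinded, pragmatic randomized clinical trial with parallel groups", and under section 3.2 patients learn their group at the first visit.

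**The concern.** The design pays for five waves of the main variable, but the named model, in its standard form, takes one outcome per patient. Two simple ways of applying it have different weaknesses.

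- **All visits stacked as separate rows.** Four correlated outcomes per patient count as independent, the standard errors are too small, and false positives rise.
- **One visit at a time.** A patient missing that visit has no outcome and leaves the analysis, even if earlier values exist. The other three follow-ups contribute nothing. In an open trial, loss may depend on early response and may differ by arm, which biases a comparison of those who remain.

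The introduction says of fibromyalgia: "The disease becomes chronic and presents in the form of flare-ups". A single visit is then a noisy picture of a patient's course, and an effect over follow-up is worth reporting beside any single-visit effect.

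**Working it through.** **1. The plan's own figure.** Inputs from section 3.2: difference 1.6, SD 1.8, two-sided alpha 0.05, power 95%, loss 20%.
- Normal approximation: n = 2 × (1.960 + 1.645)² × (1.8/1.6)² = 32.9, so 33 per arm. 33/0.8 = 41.3, so 42.
- Exact t-test: 34 per arm. 34/0.8 = 42.5, so 43, the stated number.

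So 43 already contains the 20% loss. With 34 left per arm, power for a difference in means of 1.6 is 95.1%.

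**2. If visits were pooled as independent rows.** The documents give no within-patient correlation; 0.3, 0.5 and 0.7 are assumed for the underlying score. For a yes/no outcome cut at the median, the correlation between visits is (2/π) × arcsin(ρ), the design effect for four visits is 1 + 3 × that correlation, and the true two-sided error is 2 × [1 − Φ(1.96/√design effect)].

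| Score correlation | Yes/no correlation | Design effect | Error, formula | Error, simulated |
|---|---|---|---|---|
| 0.3 | 0.19 | 1.58 | 12% | 11.5% |
| 0.5 | 0.33 | 2.00 | 17% | 14.8% |
| 0.7 | 0.49 | 2.48 | 21% | 19.4% |

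The simulation (1,500 trials per row, 43 per arm, no true effect, no dropout) used a Wald test from pooled logistic regression. With patient-level standard errors, the same data rejected in 4.3% to 5.4%.

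**3. If one visit is analysed: precision.** At 20% loss, 43 × 0.2 = 8.6, so 9 leave and 34 remain per arm. With an assumed correlation of 0.6 and baseline adjustment, the complete-case standard error at 12 months is 1.8 × √(1 − 0.6²) × √(2/34) = 0.349. A repeated-measures model gives about 0.343 at the same visit, a gain of about 2%.

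The average over four visits is more precise. Before dropout its standard error is 1.8 × √[(1 + 3 × 0.6)/4 − 0.6²] × √(2/43) = 0.226. That is a different summary, however, and gains most if the effect is roughly constant.

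**4. If one visit is analysed: bias.** Assume no true effect, random loss in the control arm, and loss in the intervention arm of the 9 patients with the lowest 1-month values. Removing the lowest 9 of 43 raises the 1-month mean of those who remain by 0.364 SD. After baseline adjustment, the bias at 12 months is about ρ × (1 − ρ) × 0.364 × 1.8:
- ρ = 0.5: 0.16
- ρ = 0.6: 0.16
- ρ = 0.7: 0.14

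Simulations agree in size. When dropout depends less sharply on the 1-month value, the bias falls to about 0.1. The range is therefore about 0.1 to 0.17 points, or 6% to 11% of 1.6. The 12-month complete-case logistic test then rejects in about 6% to 9% of trials instead of 5%. The mixed model largely removes the bias, because the 1-month value that drives dropout stays in the analysis.

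**The case against.** The strongest objection is that the text is silent rather than wrong. Section 3.3 speaks of logistic regression models in the plural. A mixed or GEE logistic model is also a logistic regression, and a condensed article commonly leaves correlation structure and missing visits to a fuller document. This stands as far as it goes: pooling is nowhere stated, and the two applications above are not the only ones. A reader might infer that the plan will inflate false positives; the documents do not support that. The 12-19% is what one unstated choice would cost.

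Second, a reader might infer that losing 9 of 43 per arm leaves the trial underpowered. It does not: the loss is already in the sample size.

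Third, large power contrasts are tempting but mix issues. At the planned difference of 1.6, with a cut for improvement that had to be assumed, 12-month logistic regression has about 87% power and the mixed model more than 99%. Baseline-adjusted complete-case means at 12 months reach that too: 1.6/0.349 = 4.58, and 4.58 − 1.96 = 2.62, so over 99%. The shortfall is the cost of dichotomising, a separate matter.

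Fourth, the dropout pattern was chosen to be one that a mixed model handles, and the bias is modest. That is true. The documents give no dropout pattern, and a mixed model would not remove bias from loss driven by unrecorded values.

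What remains is that the article does choose the class of model, twice, and that class does not by itself use the repeated measurements of the main variable.

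**Conclusion.** The point holds as a cheap improvement, not as a demonstrated error. The only between-arm model named is not connected to the four follow-ups of the main variable, and a better-suited model exists for data already being collected.

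The size depends on how the stated model would be applied:
- Pooled without correlation: about 12-19% false positives (correlations of 0.3 to 0.7, assumed).
- One visit at a time: valid standard errors and no loss of planned power for means, but three follow-ups unused and a bias of about 0.1 to 0.17 points under the assumed arm-specific dropout.

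It would overstate the case to say that most of the precision is wasted. At any one visit the gain is about 2%; the larger gain belongs to an averaged effect, which answers a different question. The case for change rests on robustness to dropout in an open trial and on using every visit.

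**What to change.** In section 3.3, state that EuroQol-5D will be analysed with a linear mixed model for repeated measures:
- all randomised patients with any follow-up value, analysed by randomised arm;
- fixed effects for arm, visit, arm-by-visit and baseline EuroQol-5D, with within-patient correlation modelled (unstructured, or a patient random effect);
- the between-arm difference with 95% CI reported at each visit and averaged over follow-up.

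If the yes/no outcome is kept, fit it as a mixed or GEE logistic model, so that visits are never treated as independent rows.

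The cost is a few lines of text. It needs no new data or patients, and SPSS, already used for the randomisation list, can fit the model. The downside is that the averaged effect is a different summary from a single late visit, so both should be reported.
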